## Abstract

**Background:**

Opposing needling is a unique method used in acupuncture therapy to relieve pain, acting on the side contralateral to the pain. Although opposing needling has been used to treat pain in various diseases, it is not clear how opposing needling affects the activity of the central nervous system to relieve acute pain. We herein present the protocol for a randomized sham-controlled clinical trial aiming to explore the cerebral mechanism of opposing needling for managing acute pain after unilateral total knee arthroplasty (TKA).

**Methods:**

This is a randomized sham-controlled single-blind clinical trial. Patients will be allocated randomly to two parallel groups (A: opposing electroacupuncture group; B: sham opposing electroacupuncture group). The Yinlingquan (SP9), Yanglingquan (GB34), Futu (ST32), and Zusanli (ST36) acupoints will be used as the opposing needling sites in both groups. In group A, the healthy lower limbs will receive electroacupuncture, while in group B, the healthy lower limbs will receive sham electroacupuncture. At 72 h after unilateral TKA, patients in both groups will begin treatment once per day for 3 days. Functional magnetic resonance imaging will be performed on all patients before the intervention, after unilateral TKA, and at the end of the intervention to detect changes in brain activity. Changes in pressure pain thresholds will be used as the main outcome for the improvement of knee joint pain. Secondary outcome indicators will include the visual analogue scale (including pain during rest and activity) and a 4-m walking test. Surface electromyography, additional analgesia use, the self-rating anxiety scale, and the self-rating depression scale will be used as additional outcome indices.

**Discussion:**

The results will reveal the influence of opposing needling on cerebral activity in patients with acute pain after unilateral TKA and the possible relationship between cerebral activity changes and improvement of clinical variables, which may indicate the central mechanism of opposing needling in managing acute pain after unilateral TKA.

**Trial registration:**

Study on the brain central mechanism of opposing needling analgesia after total kneearthroplasty based on multimodal MRI ChiCTR2100042429. Registered on January 21, 2021

**Supplementary Information:**

The online version contains supplementary material available at 10.1186/s13063-022-06066-6.

## Background

Total knee arthroplasty (TKA) is one of the most commonly used methods for the treatment of advanced knee osteoarthritis (KOA) [1] as well as one of the most common elective surgeries in the USA [2]. It can effectively relieve pain, restore knee joint function, and improve quality of life, posture, and balance [3, 4]. Nevertheless, the potential postoperative complications following TKA, such as infection, pain, venous thrombosis, and fracture, are cause for concern for both surgeons and patients; therefore, it is necessary to control and reduce the incidence of these complications [5]. In the early stage of recovery after TKA, severe acute pain will occur [6], and inadequate pain management can delay the recovery process and may be accompanied by greater risks such as poor wound healing, prolonged hospitalization, unnecessary psychological stress, and reduced satisfaction. Severe postoperative pain also increases the risk of persistent long-term pain [7–9].

There are many ways to control postoperative pain [10]. “The panel recommends that clinicians offer multimodal analgesia…combined with nonpharmacological interventions, for the treatment of postoperative pain… (strong recommendation, high-quality evidence)” [10]. In clinical practice, surgeons and anesthesiologists generally utilize opioids for this purpose [11]. However, in orthopedic patients, preoperative opioids have been shown to result in preoperative hyperanalgesia and poorly controlled postoperative pain [12]. Furthermore, in patients undergoing primary arthroplasty, preoperative opioid use is a risk factor for increased postoperative narcotic consumption [13], postoperative complications [13–18], increased length of stay [15, 18], postoperative emergency room visits [14], revision surgery [14, 19, 20], readmission [13, 14, 18], increased costs [13, 18], and inferior clinical outcomes [21, 22].

Acupuncture, which is widely accepted and applied in daily life due to its exceptional therapeutic effects [23], has been used for several thousand years in China. It is a safe treatment method without severe side effects. As a non-pharmaceutical intervention, it not only can relieve early postoperative pain, but also helps to reduce the consumption of opioid analgesics [24]. Compared with other alternative therapies, acupuncture is safer and has greater potential for postoperative pain control [25]. Electroacupuncture (EA), a combination of traditional acupuncture and modern medicine that applies various levels of stimulating currents to acupoints via acupuncture needles, is relatively common in Chinese medical clinics and has a therapeutic effect on acute and chronic pain [26, 27]. Therefore, this method may be considered as an adjunct intervention for long-term pain relief in standard non-drug therapy [28]. Acupuncture to the knee joint on the operative side can relieve acute pain after TKA, but it may be associated with surgical incision infection [29]. In a previous study, to avoid this complication, we applied opposing needling (acupuncture to the unaffected knee) for pain management after TKA [28].

Opposing needling, an ancient nine-needle method, was first reported in Huangdi Neijing. Most Chinese medical practitioners use opposing needling therapy to treat unilateral limb pain [30]. This therapy has also been used in the field of functional rehabilitation and various types of neuralgia [31]. Studies have shown that contralateral and ipsilateral acupuncture have different analgesic regulation mechanisms and that contralateral acupuncture has a superior analgesic effect [32, 33]. This is mainly reflected in the different regulatory effects on the cingulate cortex. At present, there are more and more studies on the central mechanism of acupuncture analgesia by using neuroimaging, mainly focusing on chronic pain such as migraine, low back pain, neck pain, and so on. In the field of acupuncture treatment of postoperative acute pain, there are few studies on the brain function mechanism. Although we have previously applied opposing needling in a pain management program after TKA, the specific brain mechanisms underlying this therapy remain unclear.

### Objectives

The current study protocol aims to (1) investigate the influence of opposing EA treatment on the brain activities of patients after unilateral TKA compared with that of sham opposing EA treatment and (2) analyze the possible correlations between the changes in cerebral activity and the improvement of clinical variables in each group, exploring how opposing EA modulates brain function to manage acute pain after TKA.

### Inclusion criteria

Subjects who meet the following inclusion criteria are eligible to participate: (1) aged 40–70 years and right-handed; (2) meet the Clinical Classification Criteria for Osteoarthritis of the Knee as recommended by the American College of Rheumatology; (3) scheduled to undergo initial right TKA under general anesthesia without contraindications; (4) undergone similar surgical approach; (5) American Association of Anesthesiologists Grade I or II [36]; (6) posterior cruciate-stabilizing prostheses (Smith & Nephew, London, UK); (7) postoperative X-ray shows good alignment of knee prosthesis; and (8) consciousness is clear and cognitive function is normal.

### Exclusion criteria

Patients will be excluded if they (1) abuse alcohol, drugs, or other medications that may influence brain imaging outcomes; (2) have psychiatric, neurologic, gastrointestinal, cardiovascular, infectious, immunologic, respiratory, or renal illnesses; (3) have any other chronic pain conditions or a history of head trauma with loss of consciousness; (4) have a diagnosis of rheumatoid arthritis or other leg-related pain disorders; (5) have magnetic resonance imaging (MRI) contraindications such as claustrophobia, a cardiac pacemaker, a defibrillator, heart stenting, or an intrauterine device; or (6) skin damage in the acupoint area.

### Exit criteria and management

Exit criteria include (1) participants request the suspension of the trial process, (2) severe postoperative complications (e.g., pulmonary embolism, infection), and (3) intra-treatment side effects. Participants who drop up during the trial will be treated with routine analgesia.

### Sample size

The sample size estimation for neuroimaging is different from that of classical randomized controlled trials. Compared with the evaluation of curative effect, neuroimaging studies focus more on mechanisms of the effects. Previous literature indicates that, for MRI studies, 12–15 participants in each group are sufficient [37, 38]. To obtain stable results of brain functional network analysis, the current study design requires at least 20 participants in each group. However, considering a 20% drop-out rate during the trial and the possibility of head movement artifact during the MRI scan that may render the images useless, we plan to recruit 80 participants (40 patients per group). Each group will undergo two MRI scans to investigate the different central responses between contralateral acupuncture and sham acupuncture after right TKA.

### Recruitment strategies

Participant registration will be conducted between March 2021 and January 2022. In order to include any other scientific publications, we will obtain written informed consent from all participants. When the participant is hospitalized, a trained nurse and several physiotherapists will implement the enhanced recovery after surgery approach (Fig. 1). Figure 2 presents the trial flow, including participant recruitment, eligibility screening, randomization, intervention, and outcome assessments. Figure 3 presents an overview of the trial design, conduct, review, and analysis. A completed SPIRIT 2013 checklist (Word) is presented in Additional file 1.

**Fig. 1 Fig1:**
[figure not shown]
Enhanced recovery after surgery

**Fig. 2 Fig2:**
[figure not shown]
Flow diagram of the trial. EA, electroacupuncture; op, operative; TKA, total knee arthroplasty; MRI, magnetic resonance imaging

**Fig. 3 Fig3:**
[figure not shown]
Schedule of trial enrollment, interventions, and assessments

### Randomization and blinding

An independent researcher will use statistical software SPSS 25.0 to ensure random grouping. Eligible and consenting patients with KOA who have undergone initial right TKA will be randomly assigned to the opposing EA group or the sham opposing EA group at a ratio of 1:1 (each group, *n* = 40). Random grouping steps: (1) setting random seeds, (2) generating random numbers (set range 0–1), (3) sorting grouping, and (4) obtaining random grouping results. Concealed grouping will be carried out using continuously encoded opaque envelopes containing treatment information. Only the acupuncture therapist in charge of EA treatment will be permitted to open the envelope.

All participants, physiotherapists, orthopedic surgeons, result evaluators, and data statisticians will be unaware of the trial grouping to reduce the risk of bias. To maximize the blinding of patients, an effective sham opposing EA and a pragmatic placebo needle design will be applied with adhesive pads, a dull-tipped placebo needle, and a sham electrical stimulation device (Fig. 4).

**Fig. 4 Fig4:**
[figure not shown]
Difference in the needles and acupuncture depth between the electroacupuncture and sham electroacupuncture groups. The tip of the pragmatic placebo needle (left) is blunt. The needle will be inserted into a sterile adhesive pad without puncturing the skin. The regular acupuncture needles (right) will be inserted into the skin of the corresponding acupoints through a sterile adhesive

### Patient safety

The study will be conducted in accordance with the guidelines and principles of the Declaration of Helsinki. Adverse events caused by acupuncture, such as subcutaneous hemorrhage, dizziness, or other severe events, will be dealt with immediately and recorded in detail in the case report form. Each patient will be compensated to participate in the study.

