#### Scheme of standard analgesic use

Within 48 h after TKA, participants will use a patient-controlled analgesia pump. Fentanyl (Yichang Renfu Pharmaceutical Co., Ltd., Yichang, China) will be used as an analgesic drug at a continuous infusion rate of 0.25 μg/kg/h, a bolus dose of 0.15 μg/kg, and a 10-min lockout time. In addition, all participants will begin oral administration of celecoxib capsules (Pfizer Pharmaceutical Co., Ltd., New York, USA), at a dosage of 200 mg once daily, 72 h after operation.

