#### Sham opposing EA

In the sham opposing EA group, a pragmatic placebo needle will be used [28]. As in the opposing EA group, the *Yinlingquan* (Spleen 9, SP9), *Yanglingquan* (Gallbladder 34, GB34), *Futu* (Stomach 32, ST32), and *Zusanli* (Stomach, ST36) acupoints will be selected. The blunt needle (size 0.25 × 30 mm, Hwato Brand, Suzhou Medical Appliance Factory, China) used at these acupoints will not penetrate the skin but will affix to the surface of the skin through an adhesive pad (Fig. 5). The same acupuncture manipulation as that of the opposing EA group will be used to simulate the genuine acupuncture process. A Huatuo SDZ-II EA apparatus (Suzhou Medical Supplies Factory, Suzhou, China) will be connected to these acupoints through special electrode wires without electric output. The sham needle will remain in the adhesive pad for 30 min during each treatment session. The process of sham opposing EA is similar to that of opposing EA, but the former does not involve skin penetration, needle manipulation, or electrical output. The sham opposing EA group will also undergo a 3-day treatment course consisting of 30-min sessions once daily. Both groups will be treated by experienced acupuncturists with standardized training.

To ensure treatment compliance, participants will be required to register for treatment. Throughout the trial, the participants will be treated separately to prevent communication between participants. Routine care pathways (including the use of any drugs) will be carried out as standard and will not be affected by the implementation of EA or sham EA. Participants who completed the trial will receive free elastic band and rehabilitation ball to assist in the rehabilitation of lower limb muscles. In addition, we will give them a 6-month follow-up and postoperative rehabilitation exercise guidance.

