### Adverse events of EA

The main EA-related complications include dizziness, acupuncture stagnation, acupoint hematoma, pain > 2 h after continuous acupuncture, and bleeding. Any such adverse events during the trial will be recorded.

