## Discussion

This is a randomized, sham-controlled fMRI study to explore how opposing needling acupuncture relieves postoperative knee pain by regulating brain function after TKA in patients with KOA.

In recent years, pain management has been widely used in the perioperative period as a core concept of accelerated rehabilitation surgery [54, 55]. Optimal postoperative pain management can effectively prevent and reduce adverse reactions and stress reactions. For this, multimodal analgesia should be adopted, and the development of multidisciplinary analgesia methods should be promoted [56, 57]. Acupuncture, a traditional Chinese medicine, has achieved good results in promoting analgesia after TKA [58, 59].

According to the traditional acupuncture meridian theory and the principle of acupoint adjacent treatment, SP9 and GB34 near the knee joint have been selected as the acupoints of the foot Taiyin spleen meridian and foot Shaoyang gallbladder meridian, respectively, for use in this study. In addition, we select the ST36 and ST32 acupoints of the stomach meridian of foot Yangming. In the theory of traditional Chinese medicine, spleen *qi* is the biochemical source of human *qi* and blood; therefore, these two acupoints have been selected to promote the operation of human *qi* and blood and to improve the state of *qi* and blood stasis caused by injury to the knee joint after surgery.

Opposing needling refers to acupuncture to healthy lower limbs. Increasing evidence from clinical and experimental studies shows that opposing needling has a protective effect and promotes functional rehabilitation, but its mechanism remains to be elucidated [60]. In patients who have undergone orthopedic lower limb surgery, acupuncture on the unaffected limb is more acceptable, and patient compliance is higher. Furthermore, this acupuncture method avoids direct invasive intervention in the surgical area and reduces the risk of postoperative infection to a certain extent.

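### Adverse-event recording is defined by attribution to acupuncture, so harms recorded in the two arms cannot be fairly compared

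*Protocol article*

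**What the plan says.** Two sections of the protocol article commit to recording harms, and both define the scope by cause.

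- **Patient safety:** "Adverse events caused by acupuncture, such as subcutaneous hemorrhage, dizziness, or other severe events, will be dealt with immediately and recorded in detail". The sentence goes on to name the case report form as the place of recording.
- **Adverse events of EA:** "The main EA-related complications include dizziness, acupuncture stagnation, acupoint hematoma, pain > 2 h after continuous acupuncture, and bleeding". It then adds: "Any such adverse events during the trial will be recorded".

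Other places bear on how this works in practice.

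- **Exit criteria and management** names "severe postoperative complications (e.g., pulmonary embolism, infection" and also "intra-treatment side effects". These are grounds for leaving the trial and apply to both arms. Study design and participants adds that the team will try to learn why participants withdraw.
- **Sham opposing EA** says of the sham procedure that "the former does not involve skin penetration, needle manipulation, or electrical output".
- **Randomization and blinding** lets only the treating acupuncturist open the allocation envelope and keeps participants and result evaluators unaware of group. **Data management and monitoring** gives access to the case report forms to the result evaluators alone.
- **Scheme of standard analgesic use** says that 72 h after operation "all participants will begin oral administration of celecoxib capsules". The Abstract starts the needling sessions at 72 h as well.

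**The concern.** When an event must first be judged to be caused by the intervention, the count in each arm depends on the judgement as well as on the treatment. In a sham-controlled trial the control patient receives nothing that could plausibly cause most needle injuries. Anyone who knows the allocation therefore has a reason to call a sham patient's dizziness unrelated and an active patient's dizziness related. Randomisation would make the arms comparable without any such judgement, but only if all events are collected.

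Serious postoperative events raise a second problem. Severe infection or embolism would surface as a reason for exit, not as a harm counted by arm. A non-severe infection has no stated route into the record. Falls are not mentioned, although walking tests are done before and after each session in patients who use walkers.

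The article's Background calls acupuncture safe. The trial's own harms data should be able to bear on that, and under this rule they do so poorly.

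**Working it through.** The plan states no adverse-event figure to reproduce. The check sets the sections side by side and then works through what the rule does to a count.

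**1. The five listed complications under sham.**

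| Listed event | Possible with a blunt needle and no current? |
|---|---|
| Needle stagnation | Largely not |
| Acupoint hematoma | Largely not |
| Bleeding | Largely not |
| Dizziness | Yes |
| Pain lasting over 2 h | Yes |

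Fewer events in the first three rows under sham would be a true difference between treatments, not a recording artefact. The rule does its damage in the last two rows and among unlisted events, where a background event can occur in either arm and counts only if attributed.

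**2. Who attributes.** There are two possible routes, and the article specifies neither.

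- The blinded evaluators decide. They hold the forms but do not know whether the skin was pierced or current delivered.
- The acupuncturist supplies the judgement. That person knows the allocation.

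**3. Effect on the count.** Let *b* be the proportion of patients with a background event, equal in both arms. Let *d* be the true extra proportion caused by EA. Let *a*E and *a*S be the chance that an event is attributed to acupuncture in the EA and sham arms.

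- Recorded in the EA arm: (*b* + *d*) × *a*E
- Recorded in the sham arm: *b* × *a*S
- Recorded difference: *d* × *a*E + *b* × (*a*E − *a*S)

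If blinded evaluators decide, *a*E = *a*S = *a*. The second term vanishes and the difference is *d* × *a*, which understates *d* whenever *a* is below 1. If the acupuncturist decides and *a*E exceeds *a*S, the second term adds a false excess in the EA arm. If all events are recorded, *a*E = *a*S = 1 and the difference is *d*.

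**4. Timing.** EA and celecoxib both begin at 72 h, a day after the 48 h fentanyl pump period ends, with physiotherapy under way since 24 h. This is the same in both arms, so it does not favour either. It does make any single attribution of, say, dizziness uncertain, so *a* is unlikely to be close to 1.

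**5. What full recording could show for infection.** The documents give no infection rate, so I assume 0.5% to 5%. The chance of at least one case in *n* patients is 1 − (1 − *p*)^*n*.

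- 40 patients: 1 − 0.995^40 = 18%; 1 − 0.95^40 = 87%
- 80 patients: 1 − 0.995^80 = 33%; 1 − 0.95^80 = 98%

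With no cases, the one-sided 95% upper limit is 1 − 0.05^(1/*n*): 7.2% for 0 of 40 and 3.7% for 0 of 80. Full recording would describe infection in this trial, not compare it precisely between arms.

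**The case against.** The strongest reply is that this is a condensed article. Neither section says that other events will go unrecorded, both lists are open-ended, and the full protocol or case report form may collect everything. It is fair that exclusivity is an inference. What stands is that the article does not stay silent on scope: it sets it twice, both times by attribution, with no all-cause provision anywhere.

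It can also be said that no between-arm safety comparison is planned, since adverse events are not among the outcomes and safety is not an objective. That limits the importance of the point. It does not remove it, because harms in a two-arm randomised trial will be read by arm.

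Several stronger readings are tempting and should be resisted.

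- A reader might infer that the sham arm can scarcely register an event. Dizziness, prolonged pain and side effects leading to exit can all occur there, and the recording sentence is not confined to one arm.
- A reader might infer that the unblinded acupuncturist decides what is recorded. The article does not say so, and the evaluators who hold the forms are blinded. It is a possibility left open, not a stated procedure.
- A reader might put a number on a spurious excess of events under EA. That needs an assumed background rate and full attribution in one arm with none in the other. The documents support neither, and with equal attribution the spurious part is zero.
- A reader might infer that infection and embolism go unseen. Severe cases trigger exit in both arms, withdrawal reasons are sought, and safety is discussed at team meetings. They would be known, but as dispositions and not as tabulated harms.
- A reader might infer that the trial should test the Discussion's claim that opposing needling "reduces the risk of postoperative infection to a certain extent". That claim is relative to needling the operated knee. Neither arm does so, and no recording rule would let this trial test it.

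**Conclusion.** The point holds in a limited form. Recording is tied to attribution to acupuncture or EA, no section provides for recording regardless of cause, and severe infection and pulmonary embolism appear only as exit criteria. The attribution must be made either blind, and so unreliably, or on word from the one person who knows the allocation, and so possibly differently by arm. Readers will not know which. Harms recorded under this rule therefore cannot be fairly compared between arms.

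The size cannot be stated. It depends on a background event rate and on attribution probabilities that the documents do not give. The direction is conditional too: understatement of a true difference if attribution is blind and incomplete, and a possible false excess under EA if it is not blind. The conclusion assumes that the two sections are applied as written and that no fuller document overrides them. The pain and imaging results are not affected.

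**What to change.** Reword the Patient safety and Adverse events of EA sections along these lines: *From the first session onward, every adverse event in either group is recorded whatever its presumed cause, using the same question at each session and including postoperative infection, thromboembolism and falls. Relation to acupuncture is entered separately by evaluators blind to group. Events are reported by randomised group, with the listed EA complications shown as a subset.*

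Relatedness then no longer decides whether an event counts, so an uncertain blinded judgement does little harm. Evaluators already assess patients before and after each of the three daily sessions, so the question needs no new visit.

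The cost is a change to protocol and form wording, one standard question at existing contacts, and more unrelated postoperative events to log. If the full protocol already collects all events, a sentence in the article saying so would be enough on that part.
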